### Statistical methods

Referring to earlier studies, approximately 40% of a population referred with suspected IBD will have the diagnosis confirmed according to the ECCO criteria (or comparable).^5 31^ Cost and practical issues will restrict the sample size to approximately 800 patients, with an expected 80% participation rate.

In the *diagnostic test accuracy study*, we will compare two independent binomial proportions, using the likelihood ratio (LR) statistic with a χ^2^ approximation and two-sided significance level (0.05). With an expected sample size of 640 participants (assuming a biomarker positivity-to-negativity ratio of 1 to 1), we will reach an approximate statistical power of 100%, assuming that the proportion of patients diagnosed with IBD is 80% in the biomarker positive group and 20% in the biomarker negative group. If we include 640 study participants, we will potentially (‘rule of thumb’) be able to build a multivariable statistical model with as many as 64 covariates. Thus, we will examine a variety of biochemical variables for diagnosing IBD (see Biomarkers section). The expectation is that a proportion of 100–200 preliminary biomarkers will be evaluated in this model to distinguish non-diagnostic markers and preliminary biomarkers that can be replicated. When applying a significance level of 0.05, each biomarker has a 5% risk of being replicated by chance. Thus, in the evaluation of, for example, 100–200 biomarkers, five to 10 biomarkers may be replicated by chance. In contrast, the risk of not replicating ‘true’ biomarkers with low effects is estimated to be approximately 20%. All replicated biomarkers will be built into a prediction model that will be optimised and evaluated by cross-validation. The primary hypothesis is that the biomarker signature will be able to characterise the participant population into an IBD and a non-IBD group.

In the *prognostic utility study*, we expect a sample size of 256 IBD patients and a 10% event rate for severe IBD within 52 weeks.^32 33^ If we assume a 15% event rate for the biomarker positive group and a 5% event rate for the biomarker negative group, and anticipate an even 1:1 biomarker positive-to-negative distribution, approximately 80 patients in each group will increase the statistical power above the 90% threshold.

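### Diagnostic study: markers are screened at 0.05 before the model is cross-validated, so, followed in the stated order, the cross-validated accuracy is biased upward

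*Protocol article*

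**What the plan says.** All of this is in the Statistical methods section of the protocol article, in the paragraph on the diagnostic test accuracy study.

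- **Cohort.** Cost and practical issues "restrict the sample size to approximately 800 patients, with an expected 80% participation rate", which gives the 640 used for planning. The article expects that "approximately 40% of a population referred with suspected IBD will have the diagnosis confirmed".
- **Screen.** Between 100 and 200 preliminary biomarkers are to be evaluated in a multivariable model in this cohort, to separate non-diagnostic markers from those that replicate. The level is 0.05 per marker with no adjustment, and the article accepts that "five to 10 biomarkers may be replicated by chance". It puts the risk of missing a true marker of low effect at about 20%.
- **Model and evaluation.** "All replicated biomarkers will be built into a prediction model that will be optimised and evaluated by cross-validation".
- **Claim.** The next sentence makes it the primary hypothesis that the resulting signature separates IBD from non-IBD.

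The paragraph describes no hold-out set, no split into discovery and validation parts, and no repetition of the screen within folds. The section on prognostic factor research lists LASSO, sparse PLS, random forest and deep learning for multivariable models, diagnostic ones included, but does not say how these relate to the 0.05 screen. Under Perspectives, replication in other cohorts is planned only where possible.

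**The concern.** Cross-validation gives a fair estimate only if the held-out patients played no part in building the model, and choosing the markers is part of building it. A null marker that passes 0.05 by chance does so because, in these 640 patients, its values happen to line up with the diagnoses. That alignment is present in every fold, held-out folds included. Refitting the coefficients without a fold does not remove it, because the marker is in the model only because of the alignment.

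At stake is the figure that will be read as the validated performance of the signature, to which the article ties the primary diagnostic hypothesis. Sensitivity and specificity of a single prespecified index test against the ECCO reference standard do not depend on this step.

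**Working it through.** **Inputs from the article.** 800 approached, 80% participation, 40% IBD, 100–200 markers, 0.05 two-sided per marker. The power figure uses a 1:1 marker split and assumes that "the proportion of patients diagnosed with IBD is 80% in the biomarker positive group and 20% in the biomarker negative group".

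**The article's own figures reproduce.**
- 800 × 0.80 = 640, of whom 640 × 0.40 = 256 have IBD and 384 do not.
- 640 / 10 = 64 covariates.
- Chance passes: 100 × 0.05 = 5 and 200 × 0.05 = 10.
- Power for 80% v 20% with 320 per group: 1.000.

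If all markers are null and independent, the chance that at least one passes is 1 − 0.95^100 = 99.4%, or 1 − 0.95^200 > 99.99%. A model would therefore almost always be built.

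**Hand calculation, all markers null and independent.** Let z be a marker's test statistic in all 640 patients.
1. For an unselected null marker, E[z²] = 1. For one that passes |z| > 1.96, E[z²] = 1 + 1.96 × φ(1.96)/0.025 = 1 + 1.96 × 2.338 = 5.58.
2. Given the full-data result, the expected product of the training and held-out effects is proportional to z² − 1. The −1 is what cross-validation removes. For an unselected marker nothing is left; for a selected one, 4.58 is left.
3. With k selected markers, the held-out separation is approximately D = [k × 4.58 / √(k × 5.58)] × √(1/256 + 1/384), and AUC = Φ(D/√2).
4. k = 5: D = (22.9/5.28) × 0.0807 = 0.350, so AUC = Φ(0.247) = 0.60.
5. k = 10: D = (45.8/7.47) × 0.0807 = 0.495, so AUC = Φ(0.350) = 0.64.

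The true value is 0.50.

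**Simulation.** 640 patients, 40% IBD, normal markers, stratified 10-fold cross-validation. Each data set was analysed with the screen done once on all patients and with the screen repeated inside each training fold. The fitted model was logistic, except in the rows marked †, which used a linear discriminant. The first row rests on 400 runs and the others on fewer (100–200 where recorded). Paired values are for 100 and 200 markers.

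| Assumed truth | Screen once, then cross-validate | Screen in each fold | Excess |
|---|---|---|---|
| All null, independent | 0.598; 0.636 | 0.498; 0.502 | 0.10; 0.13 |
| Ten weak true markers, each with about 80% power | 0.702; 0.717 | 0.645; 0.630 | 0.06; 0.09 |
| All null, common correlation 0.3† | 0.555–0.560 | 0.50 (true value) | about 0.06 |
| All null, common correlation 0.5 (200 markers) | 0.514 | 0.499 | 0.015 |
| One marker of planned strength, rest noise† | 0.887; 0.889 | 0.875; 0.863 | 0.01; 0.03 |

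The planned-strength marker was given a standardised difference of 1.68, which is 2 × Φ⁻¹(0.80).

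**Further checks.**
- With ten weak true markers, the once-screened model reached AUC 0.647 and 0.636 in new patients. The in-fold estimate (0.645, 0.630) is therefore close to the truth, and the other is not.
- The 80%/20% rates at 1:1 imply 0.5 × 0.80 + 0.5 × 0.20 = 50% IBD rather than 40%. At 50% the null results hardly change: 0.595 and 0.633, against 0.500 and 0.499 in-fold.
- Screening by Wald p < 0.05 in one multivariable model, closer to the article's wording, gives 0.604 against 0.499 (100 null markers).
- Correlation only within blocks of ten (0.5) gives null AUCs of 0.572 and 0.599, so the structure of the correlation matters as well as its level.

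**The case against.** **The article never says that the screen uses the full data.** This is true. The text is compressed and sits in a sample-size paragraph, a fuller analysis plan is promised before any analysis, and fold structure is normal content for such a plan. A reader might infer that the documents commit to a biased analysis, and they do not go that far. What stands is that the article is not silent: it gives the order select, build, cross-validate, with one list of passing markers counted over the whole cohort. A plan that follows this order inherits the bias.

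**LASSO, sparse PLS and random forest select during fitting.** Used alone inside the folds, they would avoid the problem. Used after a 0.05 pre-filter, they would not, and the article does not say which is meant.

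**The markers are preliminary ones to be replicated, so they are not all null.** This is fair, and it is why the all-null result is not the expected size. Prior evidence does not remove the leak, because passing is still decided on this cohort's diagnoses.

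**Noise would pass as a validated signature.** A reader might infer this, but it is too strong. With all markers null and independent, accuracy at the 0.5 cut-off is 0.610 and 0.625, against 0.60 for calling everyone non-IBD. Few would take that for a working test. The practical harm is an overstated signature rather than one invented from nothing.

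**The same flaw in the prognostic study.** A reader might extend the point there. The article gives this sequence only for the diagnostic study and describes a different prognostic analysis, so the extension is not supported.

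**The uncorrected 0.05 must be replaced by false discovery rate control.** This does not follow either. The article openly accepts 5–10 chance markers against a miss risk of about 20%. That is a trade-off the investigators may make, and stricter control would raise the miss rate.

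**Conclusion.** The point holds for the diagnostic study, in conditional form: if the stated order is followed, the cross-validated accuracy is biased upward. The direction follows from the order alone. The size depends on facts the article does not give, namely how many markers are real, how strong they are and how they are correlated. Under the assumptions shown, the AUC excess is:

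- 0.10–0.14 with all markers null and independent, which is the top of the range and not the expected value;
- 0.06–0.09 with ten weak true markers;
- about 0.05–0.07 for null markers at correlation 0.3, and about 0.015 at 0.5;
- 0.01–0.03 if one marker reaches the planned strength.

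The bias is thus small if one strong marker dominates, and material in the setting the article itself anticipates, where markers of low effect are screened in number. Using one cross-validation both to optimise and to evaluate may add further optimism, which was not quantified.

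**What to change.** Add a sentence to the diagnostic paragraph of Statistical methods, and carry it into the analysis plan. It should say that every step that uses the diagnosis (marker screening, choice of cut-offs, tuning) is repeated inside each training fold, by nested cross-validation or by a bootstrap of the whole pipeline, and that only this estimate is reported as validated performance. The same sentence should say whether the 0.05 screen precedes the LASSO, sparse PLS and tree-based models.

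The final marker list can still be drawn from all 640 patients and the 0.05 threshold can stay; only the performance estimate changes. The cost is wording and computing time. The downside is a lower reported accuracy, by roughly the amounts above.

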**Clinical trial registration number:**

NCT05414578; Pre-results.

STRENGTHS AND LIMITATIONS OF THIS STUDYAll participants included on suspicion of inflammatory bowel disease and treatment naïve.Strong international collaboration and extensive inclusion area with 11 sites in four Nordic countries.Prospective, longitudinal study design with rigorously collected biological material and data on disease activity and lifestyle.Patient heterogeneity (four countries).Ascertainment bias; as some patients with severe disease course may not be eligible for inclusion if acute treatment is initiated.

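### The prognostic study's power claim is wrong: 80 patients per group gives about 56–58% power for 15% vs 5%, not above 90%, and all 256 IBD patients give only about 76–79%

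*Protocol article*

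**What the plan says.** The prognostic paragraph of the protocol article's Statistical methods section supplies these design inputs:

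- Cohort and overall rate: "we expect a sample size of 256 IBD patients and a 10% event rate for severe IBD within 52 weeks".
- Event rates by marker status: "If we assume a 15% event rate for the biomarker positive group" and "a 5% event rate for the biomarker negative group".
- Split: "anticipate an even 1:1 biomarker positive-to-negative distribution".
- Conclusion: "approximately 80 patients in each group will increase the statistical power above the 90% threshold".

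That paragraph names neither a test nor a significance level. The only ones in the section belong to the diagnostic study, where "we will compare two independent binomial proportions, using the likelihood ratio (LR) statistic" is paired with a χ² approximation and a two-sided level of 0.05. The section on prognostic factor research makes the difference in the proportion with severe IBD between marker groups the primary prognostic analysis, so a two-proportion calculation is the right one to check.

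**The concern.** A difference of 15% versus 5% with 80 per group means 12 expected events against 4, which is too few for 90% power at conventional levels. This is the article's only power statement for the prognostic primary endpoint. It tells the reader that 160 patients would suffice and that a cohort of 256 has reserve. If the claim is wrong, a negative result for a marker could be taken as firmer evidence against it than the data can support.

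**Working it through.** **Inputs.** From Statistical methods: p1 = 0.15, p2 = 0.05, 1:1 split, n = 80 per group as claimed, and 256/2 = 128 per group as expected. The mean rate is (0.15 + 0.05)/2 = 0.10, which agrees with the stated 10%. Alpha is 0.05 two-sided, carried over from the diagnostic paragraph.

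**Pooled normal approximation.** Power = Φ[(d − 1.96·SE0)/SE1], with d = 0.10, SE0 = √(2 × 0.10 × 0.90/n) and SE1 = √((0.15 × 0.85 + 0.05 × 0.95)/n) = √(0.175/n).

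- n = 80: SE0 = 0.0474, SE1 = 0.0468. Power = Φ[(0.10 − 0.0930)/0.0468] = Φ(0.150) = **56.0%**, against a claim of more than 90%.
- n = 128: SE0 = 0.0375, SE1 = 0.0370. Power = Φ[(0.10 − 0.0735)/0.0370] = Φ(0.717) = **76.3%**.

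**Likelihood ratio χ².** The noncentrality is n × 2[0.15 ln(0.15/0.10) + 0.85 ln(0.85/0.90) + 0.05 ln(0.05/0.10) + 0.95 ln(0.95/0.90)] = 0.0579n. This is 4.63 at n = 80 and 7.41 at n = 128.

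**Other two-group methods, two-sided 0.05**

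| Method | 80 per group | 128 per group |
|---|---|---|
| Pooled normal | 56.0% | 76.3% |
| Unpooled normal | 57.1% | 77.2% |
| LR, noncentral χ² | 57.6% | 77.7% |
| LR, exact enumeration | 58.4% | 78.9% |
| Arcsine | 58.6% | 78.7% |
| Pearson, exact enumeration | 57.3% | 78.4% |
| Fisher | 48.1% | 71.2% |
| Yates | 44.1% | 71.2% |

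**Trying to recover the stated figure.**

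- One-sided 0.05 at 80 per group: 68–71%. One-sided 0.10: 79.9%.
- One-sided 0.05 with all 256 patients: 85–87%.
- Reading the 80 as a slip for 160 per group: 85.0% (pooled) to 87.1% (exact LR), two-sided. It passes 90% only if the test is also made one-sided (91% pooled), and it needs 320 IBD patients.
- A one-sample test of 80 patients, 15% against a fixed 5%, gives 90.5%. That may be where the number came from, but this is a guess, and the text describes a two-group comparison.

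**Sample size for 90%.** Pooled: n = (1.960 × √0.18 + 1.282 × √0.175)²/0.10² = 187.1, so 188 per group (376 in all). LR: 182 per group (364 in all). For 80% power the figures are 141 and 136 per group, so 256 patients miss that mark too.

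**What 128 per group can detect.** At a 10% mean rate and a 1:1 split, 16% versus 4% gives Φ[(0.12 − 0.0735)/0.0367] = 89.7% pooled, and 92.2% by exact LR.

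**Sensitivity to the event rate (assumed values).** The limitations list says that "as some patients with severe disease course may not be eligible for inclusion if acute treatment is initiated", which could lower the rate but gives no size. Keeping the threefold ratio and 128 per group, an assumed overall rate of 7% (10.5% vs 3.5%) gives 59% pooled power, and 5% (7.5% vs 2.5%) gives 45%.

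**The case against.** The arithmetic itself is not contested. What can fairly be said on the other side is this:

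- **Alpha and test are borrowed.** The prognostic paragraph states neither. True, and it should be said openly, but one-sided 0.05 still leaves the claim about 20 points short.
- **80 versus 128 is not a contradiction.** A sufficient number below the expected number is coherent. This stands: the error is only that 80 is not sufficient.
- **The 5% and 7% rates are not the plan's.** Correct. They are illustrations, and adding them is optional.
- **Marker prevalence does not clearly worsen matters.** Holding 15% and 5% fixed, a 20–30% marker-positive share gives 66–73% pooled power, but the overall rate then falls to 7–8%. Keeping the 10% rate and the threefold ratio gives 80.1% and 82.5% pooled. Imbalance alone is therefore not an argument against the design.
- **The figure did not set recruitment.** The article says cost and practical limits fixed the sample size, and much of the prognostic work is marker discovery and modelling. This limits the consequence to how results will be read. It does not make the published number right.

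**Conclusion.** The claim is wrong as written. Power at 80 per group is about 56–58% by the pooled normal and LR methods, more than 30 points below the stated threshold; Fisher or Yates would give less. The full expected cohort gives about 76–79%, short of 80% as well as 90%. A true threefold risk would be missed 42–44% of the time with 160 patients and 21–24% with 256. These results rest on two-sided 0.05, a single marker without multiplicity adjustment, complete 52-week outcomes and an exact 1:1 split at the stated rates. The article makes this as a positive numerical statement, so it is not a detail that can be left to the later analysis plan.

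**What to change.** Replace the sentence with wording such as: *With 256 IBD patients (128 biomarker-positive, 128 biomarker-negative), power to detect 15% versus 5% at two-sided 0.05 is about 77% (76–79% depending on method). At the same 10% overall rate, about 90% power is reached only for a difference near 16% versus 4%.* Delete the 80-per-group figure and the 90% claim, and state the test and significance level for the prognostic comparison, since neither is given there now. Power at lower assumed event rates, for example 7% and 5%, would be a useful optional addition.

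The cost is one corrected sentence and a less favourable power figure. Recruitment, endpoints and design do not change.

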### Comparison of measures of diagnostic accuracy

The basic measures of quantifying the diagnostic accuracy of a test will be the diagnostic OR, sensitivity and specificity measures. From these measures, we will calculate the LR, the ratio of the probability of the index test result among patients who have IBD to the probability of the same test among patients who do not have IBD (non-IBD). Since all diagnostic tests will be performed on each patient, paired data results and methods that account for the correlated binary outcomes are necessary (eg, McNemar’s test).

### Prognostic factor research (the prognostic utility study)

The primary statistical analysis will be based on the proportion of participants experiencing severe IBD among biomarker-positive versus biomarker-negative patients. The efficacy of the prognostic biomarker(s) will be considered as the proportion of the patients with different disease outcomes among the biomarker-positive patients compared with the biomarker-negative patients. The associations of the suspected important molecular biomarkers with other variables will be tested with non-parametric tests: with Spearman’s rank correlation (rs) for continuous variables and the Wilcoxon rank-sum test or Kruskal-Wallis test, including a Wilcoxon-type test for trend across ordered groups where appropriate, for categorical variables.

Logistic regression models will be utilised with individual markers as the exposure variables and composite clinical severity as the outcome (dependent variable). The analyses will be adjusted simultaneously for sex, age and prescribed therapy. Potential interactions between biomarker status (positive/negative) and specific drug type will be evaluated too. Covariates comprise of various measures within genetics, transcriptomics, microbiomes and proteomics (see Biomarkers section). We will attempt to develop prediction models containing several conventional risk factors (ie, age, sex and type of drug therapy) with or without any novel biomarkers and calculate improvements in predictive ability using risk discrimination and reclassification measures. We will use a two-stage approach that allows for the examination of centre heterogeneity through the calculation of the C-index, a measure of risk discrimination and changes within each centre before pooling results.

We will attempt to develop multivariable prediction models, relating multiple predictors for a particular individual to the probability of or risk for the presence (diagnosis of IBD at baseline) or future occurrence (prognosis) of a particular outcome, such as intestinal surgery within the first year. Predictors such as biomarkers are covariates, explored as prognostic or predictive factors. Models will be built using regularised regression methods, such as sparse Partial Least Squares (PLS) regression or Least Absolute Shrinkage and Selection Operator (LASSO), as well as tree-based machine learning approaches, such as random forest, or non-linear non-symbolic deep learning approaches, capitalising on available published data sets. Also, multiple data sets will be used for integrative analyses, to explore if combinations or interactions of variables of different kinds could aid predictive or prognostic potential of our models.

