### Biomarkers

At the time of submission, the NORDTREAT executive committee has approved projects on the following topics in relation to diagnosis and prognosis (including inflammatory intensity, disease extend, tissue damage, tissue repair activity and severe disease course): extracellular matrix proteins, microbiome, mycobiome, faecal markers, genetic risk factors, metabolomics antibodies towards microbial and autoantigens.

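### For quantitative biomarkers, a positive/negative split as the primary prognostic test probably wastes information when only about 26 events are expected; the size of the loss depends on marker shape

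*Protocol article*

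**What the plan says.** The section on prognostic factor research in the protocol article names one primary prognostic analysis: "The primary statistical analysis will be based on the proportion of participants experiencing severe IBD among biomarker-positive versus biomarker-negative patients". The sentence after it defines the value of a prognostic biomarker by the same contrast, and the drug-interaction analysis also uses positive/negative status.

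The Statistical methods section plans on that contrast: "we expect a sample size of 256 IBD patients and a 10% event rate for severe IBD within 52 weeks"; "If we assume a 15% event rate for the biomarker positive group and a 5% event rate for the biomarker negative group". It goes on to "anticipate an even 1:1 biomarker positive-to-negative distribution" and concludes that "approximately 80 patients in each group will increase the statistical power above the 90% threshold".

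The Biomarkers section lists extracellular matrix proteins, microbiome, mycobiome and faecal markers, and ends with "genetic risk factors, metabolomics antibodies towards microbial and autoantigens".

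A regression analysis is planned as well: "Logistic regression models will be utilised with individual markers as the exposure variables and composite clinical severity as the outcome". It is adjusted for sex, age and prescribed therapy. The article does not call it primary and does not say whether the marker enters as a measured value or as a status.

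**The concern.** Extracellular matrix proteins, metabolites and faecal markers are normally reported as measured quantities. Reducing such a measurement to two categories treats a patient just above the cut like one far above it, so any gradient of risk within each category is lost to the test. With 10% of 256 patients, about 26 events, there is little information to spare. The Statistical methods section says that cost and practical issues limit recruitment, so a more efficient analysis is one of the few ways left to gain power.

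A second issue arises if a cut-off has to be chosen within this cohort. The positive group would then depend on the cohort's own distribution and would not carry over to another population. The article does not say that this will happen, but neither does it fix a cut-off.

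**Working it through.** **Inputs from the Statistical methods section.** Event rates 15% and 5%; 1:1 split; about 80 per group (160 in total) for the power claim; 256 IBD patients expected; 10% overall event rate, so 0.10 × 256 = 25.6 events. Two-sided 0.05 with a likelihood-ratio test is stated for the diagnostic study only; using it here is an assumption.

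**Step 1: the plan's own power figure.** For two proportions with pooled variance under the null,

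power = Φ{ [|p1 − p2|√n − 1.96√(2·p̄·(1 − p̄))] / √(p1(1 − p1) + p2(1 − p2)) }, n per group.

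Here √(2 × 0.10 × 0.90) = 0.4243 and √(0.1275 + 0.0475) = 0.4183.

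- n = 80: (0.8944 − 0.8315)/0.4183 = 0.150, power 56%. Unpooled, arcsine, likelihood-ratio and exact versions give 57–59%; one-sided versions give 68–69%.
- n = 128 (all 256 patients): (1.1314 − 0.8315)/0.4183 = 0.717, power 76%; the other two-sided versions give 77–79%.
- 90% power needs (0.8315 + 1.2816 × 0.4183)²/0.10² = 187.05, so 188 per group (376 in total).

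The stated figure above 90% is not reproduced by any version.

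**Step 2: information lost by a median split.** For a normal marker with a linear effect, the split keeps 2/π = 0.637 of the information, a loss of 36%. At 256 patients that is like setting aside 0.363 × 256 = 93 of them. Multiplying n per group by π/2 in the Step 1 formula approximates the continuous test: 80 × 1.571 = 125.7 gives 76%, and 128 × 1.571 = 201.1 gives 92%.

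**Step 3: simulation.** A continuous marker was calibrated so that its upper and lower halves have exactly 15% and 5% risk. For a standard normal marker this gives intercept −2.419 and log-odds 0.764 per SD. Each case had 20,000 simulated data sets and a two-sided test at 0.05. The continuous test was the likelihood-ratio test in univariable logistic regression; the split was at the sample median.

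| Assumed marker and effect | N | Continuous | Median split |
|---|---|---|---|
| Normal, log-linear | 160 | 79% | 57–58% |
| Normal, log-linear | 256 | 93% | 78–79% |
| Uniform, log-linear | 160 | 72% | 57% |
| Uniform, log-linear | 256 | 89% | 78% |
| True step at the median | 160 | 38% | 51–53% |
| True step at the median | 256 | 58% | 74% |

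Ranges for the split reflect the choice between Pearson and likelihood-ratio tests.

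**Step 4: other cut-offs.** For the normal log-linear marker at 256 patients, the likelihood-ratio test after a cut at the 67th, 75th or 90th percentile has power of about 80%, 78% and 67%, against 93% for the continuous test. The loss in that case is not peculiar to the median.

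**Not modelled.** Adjustment for sex, age and therapy, missing outcomes, and multiplicity across many markers. With about 26 events these would probably lower power for either analysis.

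**The case against.** The strongest reply has four parts.

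- **The premises are not in the text.** The article does not say that the markers are continuous or that positivity means above the median. The 1:1 ratio is a planning expectation, not a cut-off rule. Genetic factors and some antibody results may be naturally binary, and definitions of positivity can properly wait for the promised statistical analysis plan. This stands: the loss must be given as conditional, and the absence of a cut-off is not itself a fault.
- **The study already plans suitable models.** Marker-level logistic regression is specified, and the penalised and tree-based prediction models need no cut-off. This stands in part. The regression is not the primary analysis and its marker scale is not stated, so the primary inference still rests on the split.
- **A binary contrast has a use.** The cohort runs alongside a biomarker-stratified randomised trial, where patients must be classified, and event proportions by status address that directly. This stands, so it would be wrong to say that the split brings no benefit. It supports keeping the proportions as a display more than making them the primary test of association.
- **The continuous test can lose.** If risk steps at a threshold, power at 256 falls to 58%, against 74% for the split. This stands and is a real cost.

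A reader might also infer that the continuous analysis would restore the power above 90% that the article claims. The figures do not support that. The claim is made for about 80 per group, and at 160 patients the continuous test gives 79%, 72% or 38% depending on shape. Among the shapes tried, it passes 90% only with all 256 patients and a normal, log-linear marker.

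**Conclusion.** The point holds as a recommendation on efficiency. The article fixes a positive/negative comparison as the primary prognostic analysis, although several approved marker classes are normally quantitative and events are few. For a normal, log-linear marker split at the median, moving to the continuous scale raises power by about 14 percentage points at 256 patients (79% to 93%) and about 21 at 160 (58% to 79%). For a uniform marker the gain at 256 is about 11 points (78% to 89%). Under a true threshold at the cut it is a loss of about 16 points (74% to 58%). Marker shape, cut-off and significance level are assumptions that the article does not settle.

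The power statement in the Statistical methods section is wrong whatever scale is chosen (about 56–59% at 80 per group for the planned comparison) and has to be restated separately.

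**What to change.** In the section on prognostic factor research:

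- For quantitative markers, make the primary test the logistic coefficient of the marker on its continuous scale, log-transformed if skewed and expressed per SD, with a spline term to check for non-linearity.
- Keep severe-IBD proportions by positive/negative status as a secondary display, using cut-offs fixed outside this data set.
- Leave inherently binary markers binary.
- State the marker scale in the marker-level logistic regression already planned.

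Separately, restate the power: about 76–79% for the binary comparison with all 256 patients, or 188 per group for 90%.

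The cost is a change of wording before any analysis, with no new data. The downside is reliance on a roughly monotone, log-linear relation: under a true threshold effect the continuous test loses power, and with about 26 events a spline check can reveal only marked departures. Clinicians will still need the cut-off table.
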